## Abstract

**Background:**

The ACTION study (*Attention deficit hyperactivity disorder Controlled Trial Investigation Of a Non-stimulant) *is a multi-center, double-blind, randomized cross-over trial of the non-stimulant medication, Atomoxetine, in children and adolescents with attention deficit hyperactivity disorder (ADHD). The primary aims are to examine the efficacy of atomoxetine for improving cognition and emotional function in ADHD and whether any improvements in these outcomes are more pronounced in participants with comorbid anxiety; and to determine if changes in these outcomes after atomoxetine are more reliable than changes in diagnostic symptoms of ADHD. This manuscript will describe the methodology and rationale for the ACTION study.

**Methods:**

Children and adolescents aged 6 - 17 y with ADHD will be enrolled. Clinical interview and validated scales will be used to confirm diagnosis and screen for exclusion criteria, which include concurrent stimulant use, and comorbid psychiatric or neurological conditions other than anxiety. Three assessment sessions will be conducted over the 13-week study period: Session 1 (Baseline, pre-treatment), Session 2 (six weeks, atomoxetine or placebo), and Session 3 (13 weeks, cross-over after one-week washout period). The standardized touch-screen battery, "IntegNeuro™", will be used to assess cognitive and emotional function. The primary measure of response will be symptom ratings, while quality of life will be a secondary outcome. Logistic regression will be used to determine predictors of treatment response, while repeated measures of analysis will determine any differences in effect of atomoxetine and placebo.

**Results:**

The methodology for the ACTION study has been detailed.

**Conclusions:**

The ACTION study is the first controlled trial to investigate the efficacy of atomoxetine using objective cognitive and emotional function markers, and whether these objective measures predict outcomes with atomoxetine in ADHD with and without comorbid anxiety. First enrollment was in March 2008. The outcomes of this study will be a significant step towards a 'personalized medicine' (and therefore a more efficient) approach to ADHD treatment.

**Trial registration:**

Australian and New Zealand Clinical Trials Registry ANZCTRN12607000535471.

## Background

Attention deficit hyperactivity disorder (ADHD) affects at least one child or young person in every classroom worldwide, with prevalence estimates ranging between 2 and 16% [1]. It is the most common psychiatric disorder in children and adolescents, and continues into adulthood in a majority of cases [2]. Problems experienced by children and adolescents with ADHD include difficulties with sustaining attention and/or hyperactivity/impulsivity. These problems impact unfavorably on the young person's everyday functioning [3], as well as the health-related quality of life of themselves and their families [4].

Stimulant medications are the most common pharmacologic treatment for ADHD [5], acutely improving symptoms in 60 - 90% of patients [2,6-8]. However, when stimulant drugs are not effective, or when there are contraindications to stimulants, non-stimulant drugs are a viable alternative. Increasingly, non-stimulant medications such as atomoxetine (ATMX) are considered when comorbid conditions, such as anxiety, are present [9]. ATMX is purported to be a viable alternative to stimulant treatment for ADHD, with particular efficacy for children and adolescents with ADHD who are prone to problems with inhibition, anxiety and substance abuse [10].

ATMX has been approved by the US Food and Drug Administration for the treatment of ADHD [7], and has a demonstrated response rate of up to 63.5% [11-13], comparable to that of stimulant treatment [14]. Compared to stimulant drugs, ATMX has a lower potential for abuse or misuse [7,15], and has the advantage of once daily dosing and continuous coverage [15]. To date, the focus has been on efficacy studies, to determine if treatment with ATMX produces improvement in diagnostic ADHD symptoms. Symptoms are assessed using well-established rating scales, including the ADHD Rating Scale IV - Parent version (ADHD-RS IV) score [3,11,16-28], Clinical Global Impressions (CGI) score [17,29], and Connors' Parent and Teacher Rating Scales: Short version [13], and the Parent-rated Hyperactivity/Impulsivity Swanson Nolan and Pelham ratings [29]. In terms of the effect of ADHD medications on objective cognitive outcomes, one cross-sectional study using historical data indicated that young people who were medicated for ADHD (with either ATMX, methylphenidate or amphetamine) performed superiorly on objective cognitive tests compared to their non-medicated ADHD counterparts, although their performance remained poorer than that of non-ADHD controls [30]. To our knowledge, there have been no controlled trials undertaken to determine: 1) if ATMX has efficacy for improving cognition; and 2) if response to ATMX is predicted by other measures of cognition in ADHD, with and without comorbid anxiety. The ACTION study has been designed to address this issue.

The ACTION study will be a double-blind, randomized, controlled cross-over trial, to assess ADHD at baseline, and after treatment with either ATMX or placebo. At each assessment point clinical ratings of symptoms will be acquired. The ACTION study will assess cognition using a standardized, computerized battery called 'IntegNeuro™" (Brain Resource Ltd., Sydney, Australia and San Francisco, USA). IntegNeuro™ has been validated and established in ADHD [1,31,32], thereby providing a basis for future studies seeking to extend or replicate our findings. Cognitive markers from IntegNeuro™ have been found to identify ADHD with high sensitivity and specificity [1]. These markers also correlate with brain function assessed by both EEG and heart rate variability [1].

The findings from the ACTION study will help support a more personalized approach to treatment options available for children and adolescents with ADHD by examining the efficacy of ATMX in improving both subjectively-rated symptom measures and objectively-assessed performance in ADHD. It will also provide evidence about which objective cognitive markers relate to ATMX response in ADHD, and how anxiety moderates ATMX response. An evidence-base of this kind may help support clinicians in making decisions about if and when to consider non-stimulants as an alternative to stimulants or non-pharmacologic treatments in each individual child or adolescent.

The primary aims of the ACTION study are to:

1. Assess whether ATMX has efficacy in improving cognition and emotional function in children and adolescents with ADHD.

2. Assess whether presence of co-morbid anxiety influences the response to ATMX in children and adolescents with ADHD in relation to cognition and emotional function.

3. Ascertain the reliability of cognitive and emotional function changes after ATMX compared to clinical symptoms of ADHD, and how these correlate with symptom changes. Please refer to Section 5 for more detail.

The methodology for the ACTION study will be detailed in this manuscript.

## Methods/Design

### 1. Study regimens

Eligible and consenting participants will complete rating scales and a computer-based test battery to assess cognitive performance. Figure 1 shows the schema for the ACTION study, which is a randomized double-blind cross-over study. After baseline assessment, participants will be randomized to receive either ATMX (brand name: Strattera) or placebo (starch powder with silicone 5% in a gelatin capsule) first, for six weeks (Phase A), before undergoing a one-week "washout" period (no capsules). Cross-over will occur after this washout period, and participants will receive the other compound (i.e., the compound they did not receive during Phase A) over a second six-week period (Phase B). Baseline (Session 1) assessments will be repeated at all time-points. ATMX doses will be based on the participant's weight, according to five pre-determined weight groups, covering the predicted weight ranges from 18 to 80 kg (Figure 2). Both the ATMX and the placebo capsules will look identical, and were purchased from Eli Lilly Australia.

**Figure 1 F1:**
[figure not shown]
**Illustration of the ACTION study schema**. W = washout period. Eligibility assessment (screening) included the ADHD-RS IV and ADISC. Sessions 1, 2, and 3 included ADHD-RS IV, CPRS-R, DASS, BRISC, CGI, PedsQL (parent and teenager reports), and the IntegNeuro™battery. The WPREMB-R was to be done on a weekly basis during Phases A and B.

**Figure 2 F2:**
[figure not shown]
**Atomoxetine dosage schedule**. Week 1 is the initiation dose, with approximately 0.5 mg.kg^-1 ^for each patient group; weeks 2-6 reach the target dose of approximately 1.2 mg.kg^-1 ^for each group (with minimum dose of 1.0 mg.kg^-1 ^and maximum dose of 1.4 mg.kg^-1^).

Randomization will be performed by a hospital biostatistician using a centralized, pre-determined pair-wise randomization technique, ensuring an even allocation of participants to receiving ATMX or placebo first; while also taking into account the expected ratios across the five weight groups (Figure 2). Once the randomization list has been generated, the hospital biostatistician will forward a copy of the master list to the compounding chemist responsible for packaging and labeling the blister cards for the study. The investigators, referring clinicians, and the participants will remain blinded to group allocation. All capsule packages will be prepared prior to the commencement of the trial, and packages will be dispensed according to the pre-determined randomization master list. As each participant enters the study, they will be allocated a study ID code in the order of numerical sequence. The corresponding blister cards will be labeled with the ID codes and corresponding study phase only. The participating clinicians, investigators, and the participants will be blinded to group allocation until the completion of the study.

#### 1.1. Treatment delivery

The dose schedule for ATMX will be based on recommendations from clinical practice and previous literature (Figure 2) [18,33]. In addition to the drug blister packs, a personalized "Take Home Package" booklet will be provided to parents/guardians of the participants, which will include a Day Counter log book to help parents keep track of their child's compliance (via daily tick boxes parents can mark off whenever their child takes their daily dose). Participants will be asked to take their capsules at the same time each morning. Drug blister packs and "Take Home Package" booklets for use during Phase A and B will be given to the parents at the end of Session 1 and Session 2 respectively. At the subsequent appointment, parents will be required to return their completed "Take Home Package" booklet, along with the drug blister packs regardless of their child's compliance, to enable the investigators to record any missed doses.

#### 1.2. Study participants

Figure 3 lists the inclusion and exclusion criteria for the ACTION study. Eligibility criteria include normal body mass for age and gender [34], age of 6 to 17 years (inclusive), and a primary diagnosis of ADHD. Both boys and girls will be enrolled into the study. The presence of any of the exclusion criteria listed in Figure 3 will preclude the participant from enrolling into ACTION.

**Figure 3 F3:**
[figure not shown]
**Inclusion and Exclusion criteria for the ACTION study**. ADHD = attention deficit hyperactivity disorder; DSM-IV = Diagnosis and Statistical Manual of Mental Disorders, Edition 4.

### 2. Participant study visits

#### 2.1. Screening (pre-Baseline)

Potentially eligible patients will undergo a clinical examination by a participating clinician. A primary diagnosis of ADHD will be based on *Diagnostic and Statistical Manual of Mental Disorders - Fourth edition *criteria [35]. The ADHD-RS IV will be used to confirm ADHD diagnosis, ADHD subtype, and to assess symptom severity. Additionally, the Anxiety Disorders Interview Schedule for Children (ADISC) [36] will be used to assess the presence of comorbid conditions. The ADHD-RS IV and ADISC scales are detailed in Section 4. They have been shown to have excellent reliability [36], validity [37], and medium-to-high specificity and sensitivity [38] in children and adolescents. The purpose of the Screening visit will be to confirm a primary diagnosis of ADHD, to determine symptom ratings, and eligibility for the study, as determined by participating clinicians.

Participants deemed eligible for the ACTION study will undergo a two-week washout period prior to Baseline testing (Session 1) if they are taking any ADHD medication at the time of Screening. Subsequent visits occur at weeks six and 13. Appointments will be confirmed over the telephone at least one day prior.

#### 2.2. Session 1 (Baseline; 0 weeks)

Prior to attending assessment sessions, participants will be asked to refrain from consuming caffeine that day (including coffee, chocolate milk, caffeinated soft-drinks).

Assessments will include cognitive and emotional function tasks using IntegNeuro™, body mass, and validated parent-reported scales for ADHD symptom severity and self-report questionnaires (Section 4). On average, assessments will take the participants approximately two hours to complete. Upon completion of Session 1, parents will be given their child's first course of study capsules and a "Take Home Package" booklet as mentioned above in 1.1.

#### 2.3. Session 2 (6 weeks; post-Phase A)

The assessments undertaken at Baseline (Session 1) will be repeated at Session 2. Parents will be reminded to return their child's capsule blister packs and "Take Home Package" booklet, so that the investigators can record compliance to the study drugs during each study phase. As with Session 1, on completion of Session 2 parents will be provided with their child's next course of study capsules and a second "Take Home Package" booklet for use during Phase B of the study.

#### 2.4. Session 3 (13 weeks; post-Phase B)

The assessments undertaken at Session 2 will be repeated at Session 3, with the exclusion of the provision of capsule blister packs and "Take Home Package" booklets.

#### 2.5. Ethical considerations

The ACTION study will be conducted according to the principles of the Declaration of Helsinki 2008, and International Conference on Harmonization (ICH) guidelines. Investigators ensure that "Good Clinical Practice" principles will be adhered to, as outlined in 21 FDA Code of Federal Regulations CFR 312, subpart D, "Responsibilities of Sponsors and Investigators," 21 CFR, part 50, 1998, and 21 CFR, part 56, 1998.

Institutional Review Board (IRB) approval is obtained prior to patient enrolment at any clinical site. All protocol modifications will be submitted to each IRB for approval before implementation. Prior to undertaking any study-related procedures, investigators will obtain written informed consent from each study participant after verbal and written explanation of study aims, methods, and potential hazards and benefits.

#### 3.2. Site selection/training/recruitment

Clinical sites were selected based on the likelihood of meeting recruitment goals and executing the protocol. During a site initiation visit, CTCs at each site will be trained in protocol implementation and data collection methods. CTCs will work closely with participants and clinicians, ensure that all instruments are completed by participants, and function as study coordinators (i.e., liaise among sites, data management at their own site, and ensure the smooth operations of the study at their site).

#### 3.3. Enrolment/randomization

Patients are referred to the ACTION study by participating clinicians, by faxing completed Clinical Package forms (containing basic demographic details, body mass; and completed ADHD-RS IV and ADISC) to their local CTC. The site's CTC will contact the interested patient's parent to formally invite them to the study, and provide additional information and consent forms.

### 4. Data collection

#### 4.1. Screening measures

Attention Deficit Hyperactivity Disorder Rating Scale-IV (ADHD-RS IV) [39] The ADHD-RS IV will confirm DSM-IV diagnosis and subtype of ADHD, indicated by a score >1 in six or more items in the Inattentive and/or Hyperactive-Impulsive sections of the scale. If a DSM-IV diagnosis cannot be confirmed using the ADHD-RS IV, the participant will be excluded. Total scores will be used as a measure of symptom severity.

Clinicians will also undertake the Anxiety Disorders Interview Schedule for DSM-IV: Child Version (ADISC: Parent Interview Schedule) [36]. Scores of ≥4 for any of the domains are indicative of a positive diagnosis. Participants will be categorized as having either ADHD + comorbid anxiety (i.e., Separation anxiety disorder, Obsessive compulsive disorder, and/or Generalized anxiety disorder [36]); or ADHD without anxiety (which includes those with other comorbidities excluding anxiety). The number of diagnosed comorbidities in total, including anxiety and others, will also be recorded.

#### 4.2. Baseline (Session 1), Session 2 and Session 3 measures

##### 4.2.1. ADHD symptom severity

At each testing session parents will complete the ADHD-RS IV, as a measure of ADHD symptom severity.

Parents will also rate symptom severity on the Conners' Parent Rating Scale - Revised (Long version; CPRS-R) [40]. The CPRS-R ratings will provide a second assessment of symptom severity, providing a within-study check on the consistency of symptom ratings. T-scores for all 13 subscales will be recorded, where larger T-scores indicate greater impairment.

The secondary outcomes of ACTION will be the relationships between the primary cognitive measures and ratings obtained from the ADHD-RS IV and CPRS-R.

##### 4.2.2. Self-reported negative feelings and self regulation

Negative feelings of anxiety, depression and stress will also be assessed via self-report, using previously established scales. The Depression Anxiety and Stress Scale (DASS) [41] has been established in 6 to 18 year olds with ADHD [42], and a child-worded version of this scale has been validated against the original in the same children completing both original (with parental help as needed to understand questions) and child version, in a randomized within-subjects design [43]. The DASS questionnaire will be scored for three domains: Depression, Anxiety, and Stress.

To assess state as well as trait anxiety, the State-Trait Anxiety Inventory (STAI) [44] or STAI for Children (STAIC) [45] will be used. The STAIC is suitable for use in children aged 6 to 14 years, while the STAI is suitable for those aged >14 years. The questionnaires provide scores on both State anxiety and Trait anxiety [46] and will be used at all three laboratory-based sessions.

To complement the scales assessing negative feelings, an established measure of self-regulation (the BRISC) will be used, which captures risk for brain health versus resilience and capacity for seeking social support [47]. The BRISC has been normed in 6 to 92 year olds [47], and there is good correspondence between child and adult-worded versions [41]. The BRISC score of Negativity Bias identifies a spectrum of brain health disorders (particularly anxiety and depression) with 87% sensitivity; and it is inversely related to Emotional resilience and social skills capacity (data not yet published). The validation study also established the convergence between this scale and a child-worded version in the same randomized within-subjects design [43]. The three BRISC scores are Negativity bias, Emotional resilience and Social skills.

#### 4.3. Other symptom measures

To further explore the secondary aims of the study, other measures of ADHD symptoms will be included at each assessment session.

##### Clinical Global Impression (CGI) scale [48]

The CGI Severity scale will be used at Session 1, based on the opinion of the investigator; while the CGI Improvement scale will be used at both Session 2 and Session 3, taking into account the opinions of both the investigator and the parent. Rating scores for each time-point will be recorded.

##### Pediatric Quality of Life Inventory (PedsQL) - Parent report, Version 4.0 [49]

The PedsQL - Parent reports for young children (8 to 12 years old) and adolescents (13 to 18 years old) were utilized at all three time-points to assess the health-related quality of life, based on the opinion of the parent. The two summary (mean) scores of Physical health (Physical health items) and Psychosocial health (Emotional, Social, and School functioning items) will be recorded.

##### PedsQL - Child report and PedsQL - Teenager report [49]

The PedsQL - Child report will be given to participants aged 8 to 12 years, while the PedsQL - Teenager report will be provided to those aged 13 to 18 years of age. Similarly to the PedsQL - Parent report, the summary scores for Physical health and Psychosocial health will be recorded for analysis.

##### Weekly Parent Rating of Evening and Morning Behavior - Revised (WPREMB-R)

This questionnaire was developed by Eli Lilly Pty. Ltd. for monitoring morning and late afternoon/evening behavior in children and adolescents with ADHD who are being treated using ATMX [50]. Six copies of the WPREMB-R will be included in the "Take Home Package 1" booklet (Phase A), and seven will be included in the "Take Home Package 2" booklet (Phase B), so that parents can complete the questionnaire at the start of each week during these phases of the study. The maximum possible score obtainable is 33, which is indicative of poorer ADHD behavior. Mean WPREMB-R scores will be calculated and recorded for both Phase A and Phase B. Missing responses in any week will exclude the participant's data for that study phase, since the scoring method of this questionnaire does not permit adjustment for missing information.

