### 5. Research endpoints

The primary endpoint will be clinically significant improvement in cognition and emotional function after ATMX treatment assessed using IntegNeuro™ (Table 1); and in ADHD symptoms (ADHD-RS IV, CGI, WPREMB, and CPRS-R subscales: Cognitive problems/inattention, Hyperactivity, Conners' ADHD index, CGI restless-impulsive, CGI total, DSM-IV inattentive, DSM-IV hyperactive-impulsive, and DSM-IV total). Further analyses will be undertaken to compare the differences in ATMX treatment effects between participants with and without comorbid anxiety; and between ADHD subtypes.

Part of the novelty of this trial lies in our utilization of objective assessments for cognition and emotional function. As such, we will also determine if our objective measures predict response to ATMX in ADHD, and in patients with comorbid anxiety. Treatment response is defined in Section 7.3.2.

The secondary endpoints will be improvements after ATMX treatment in quality of life (PedsQL - self and parent); emotional states and self-regulation (DASS-BRISC); and state and trait anxiety (CPRS-R subscales: Anxious-shy, STAI and STAIC). Previous ADHD treatment with stimulant medication and comorbid anxiety will be included as covariates.

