#### 7.3. Data analysis

The ACTION study will adopt an all available data analytical approach, meaning that all data obtained will be included in analyses, regardless of adherence to the study. Accordingly, there will be no imputation of missing data. For all analyses, a *p *value of <0.05 will be considered statistically significant.

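### One missing weekly response deletes a child's whole phase of WPREMB-R data, contrary to the all-available-data rule, and the plan does not say whether the seventh Phase B form is averaged in

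*Protocol article*

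**What the plan says.** Section 4.3 (WPREMB-R) supplies six forms in the Phase A booklet and seven in the Phase B booklet, so that parents can "complete the questionnaire at the start of each week during these phases of the study". The summary is one number per phase: "Mean WPREMB-R scores will be calculated and recorded for both Phase A and Phase B". The missing-data rule is "Missing responses in any week will exclude the participant's data for that study phase", and the reason given is "since the scoring method of this questionnaire does not permit adjustment for missing information".

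Section 7.3 sets the general policy: "all data obtained will be included in analyses, regardless of adherence to the study", with no imputation.

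The standing of the scale is mixed. Section 5 places it inside the primary endpoint: "and in ADHD symptoms (ADHD-RS IV, CGI, WPREMB, and CPRS-R subscales". Section 4.3 opens with "To further explore the secondary aims of the study, other measures of ADHD symptoms will be included at each assessment session". Sections 4.4 and 7.1 treat inhibition and emotion identification as the primary outcomes, and the trial is sized on those two.

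On timing, Section 1 gives each phase six weeks with a one-week washout between them. Section 2.1 puts the later visits at weeks 6 and 13. Sections 1.1 and 2.3 have the second booklet handed out at Session 2.

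**The concern.** The exclusion rule is fixed in the article, so it is not a detail left to an analysis plan, and it cannot hold together with Section 7.3. One gap in one week discards up to six other complete forms. Because a within-child comparison needs both phases, the loss compounds over 13 forms. The families who remain are those who never missed a response, and they may differ from the rest in ways related to the child's behavior.

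The second issue is which weeks are compared. A six-week phase has six week-starts, so a seventh form does not fit the stated schedule. If it covers an untreated week and is averaged in, the two phase means describe unlike windows and the treatment contrast shrinks. The article does not settle this.

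**Working it through.** **1. The two rules side by side.** Section 4.3 deletes observed, complete forms, while Section 7.3 includes all data obtained. The scoring reason concerns how a score is built when information is missing. It can explain why an incomplete form gets no score. It says nothing against averaging the forms that are complete, and doing so imputes nothing, so it also respects Section 7.3.

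**2. Data loss.** Inputs: 6 and 7 forms (Section 4.3) and a planned minimum of 152 children (Section 7.1), used only to turn shares into counts. The figure of 152 cannot be reproduced, because the article gives no mean difference or standard deviation, and it was not derived for this scale. Let q be the chance that a form has a missing response. The article gives no q, so a range is assumed, with independence between forms. Retention is (1−q)^6 for Phase A, (1−q)^7 for Phase B and (1−q)^13 for both.

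| q (assumed) | Phase A kept | Phase B kept | Both kept | Of 152 |
|---|---|---|---|---|
| 2% | 88.6% | 86.8% | 76.9% | 117 |
| 5% | 73.5% | 69.8% | 51.3% | 78 |
| 10% | 53.1% | 47.8% | 25.4% | 39 |

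If families differ in their miss rate, these shares are floors at the given average q. At the other extreme, where a share q of families misses everything and the rest miss nothing, 1−q keep both phases: 98%, 95% and 90%.

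**3. The same q with complete weeks averaged.** As an illustration, take six on-treatment forms per phase and require at least four complete (an assumed threshold). The share with both phases usable is [P(X ≥ 4)]², with X binomial(6, 1−q): 99.97%, 99.6% and 96.9%, or about 152, 151 and 147 of 152.

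**4. The seventh form.** From Session 2 (week 6) to Session 3 (week 13) is 13 − 6 = 7 weeks, which equals one washout week plus six treated weeks. Washout is therefore the natural place for the extra form, but the article does not say so. It also does not say whether a form rates the current or the preceding week. Assume the same effect in every treated week, none otherwise, and equal numbers in the two sequences. The share of the true contrast that remains is then:

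| A form rates | All seven Phase B forms averaged | Washout-week form left out |
|---|---|---|
| Current week | Atomoxetine first 1; placebo first 6/7; mean 13/14 = 0.93 | 1 (no dilution) |
| Preceding week | Atomoxetine first 5/6 − 1/7 = 0.690; placebo first 5/7 = 0.714; mean 0.70 | 5/6 = 0.83 in both sequences |

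In the lower row, the first Phase A form rates the week before treatment. The first form in the second booklet rates the last week of Phase A, and the next one rates the washout.

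**The case against.** The strongest reply concerns dilution. A reader might infer from the six and seven copies that the plan averages six forms against seven and so dilutes the contrast. The article does not support that as a statement of fact. It gives booklet counts and, separately, one mean per phase. Section 1 defines Phase B as six weeks starting after the washout, and the Figure 1 caption places the scale within Phases A and B, so a washout form can be read as outside the Phase B mean. The 70% figure also needs a recall window that the article does not give. With even allocation to the two sequences, any dilution on these readings shrinks the contrast and does not reverse it. All of this stands, and the dilution point is reduced to an ambiguity that should be closed.

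It is also fair that the loss figures rest on an assumed miss rate and that independence leans them toward the pessimistic end. The rule touches one symptom scale, not the markers on which the trial is sized, nor the responder analyses, which Section 7.3.2 bases on ADHD-RS IV and CPRS-R.

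None of this answers the conflict between Sections 4.3 and 7.3, or the gap between the scoring reason and the deletion of complete forms.

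**Conclusion.** The exclusion rule is wrong as written. It contradicts Section 7.3, and its own rationale does not reach the complete forms that it deletes. With independent misses at an assumed 2%, 5% or 10% per form, about 77%, 51% or 25% of children keep both phases. Clustering raises those shares, but the children kept are still selected on form completion. No power loss is claimed, because the article gives no effect size or variability for this scale.

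What the seventh form does is unclear; it is not shown to be wrong. The contrast is undiluted if that form is left out and forms rate the current week. About 93% remains if a washout form is averaged in, and about 70% if forms rate the preceding week and all are averaged.

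The point is worth correcting because Section 5 lists the scale in the primary endpoint. Its weight is limited by the secondary placing in Section 4.3 and by a sample size built on other markers.

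**What to change.** 1. Delete the any-week exclusion in Section 4.3. Compute each phase mean from the complete weekly forms, and state the minimum number required, if any. A mixed model on the weekly scores is an option, not a necessity.
2. State which week each form rates and which forms enter each mean. Use only forms that rate on-treatment weeks, matched across the phases, and leave out any washout form. If the second booklet starts at the washout and forms rate the current week, these are Phase A forms 1–6 and Phase B forms 2–7. If forms rate the preceding week, they are Phase A forms 2–6 and Phase B forms 3–7, which cover treated weeks 1–5 of each phase. In that case the first Phase A form is pre-treatment and can be kept for the baseline comparisons in Section 7.3.3.
3. Make the standing of the scale the same in Sections 4.3 and 5.

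The cost is wording in the analysis section. No extra forms or visits are needed. The downside is slightly noisier phase means for children with few complete forms.
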